#### 9.4.1.1 Dose-Finding of Single Agent MP0317

A 2-parameter BLRM will be used for dose-escalation. All information currently available about the dose-DLT relationship of MP0317 is summarized in a prior distribution (Table). This prior distribution is then updated after each cohort of patients with all of the DLT data available in the DDS from the current study. Once updated, the distribution summarizes the probability that the true rate of DLT for each dose lies in the following categories:

- [0,16%) underdosing
- [16%,33%) targeted toxicity
- [33%,100%] excessive toxicity

The EWOC principle mandates that any dose of MP0317 that has more than a 25% chance of being in the excessive toxicity category is not considered for the next cohort. After a clinical synthesis of the available toxicity information (including AEs that are not DLTs), PK, pharmacodynamic and efficacy information as well as the recommendations from the Bayesian model, the DERC will determine the dose level for the next cohort at a dose-escalation meeting. In all cases, where there is a change in dose level to be administered to the next enrolled patients, a new model will be defined using a Meta-Analytic-Predictive prior, based on the observed data.

The frequency of DLTs will be tabulated by dose for patients in the dose-escalation part and information about the DLTs will be listed by dose.

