#### 9.4.1.2 Bayesian Logistic Regression Model for MTD Determination

The objective of the design is to determine the MTD defined as the highest dose with less than 25% risk of the true DLT rate being above 33%. The dose-finding will be guided by a Bayesian 2-parameter logistic regression model with overdose control. These designs have been shown to be superior regarding the precision of MTD determination compared to 3+3 designs and have been particularly endorsed by the FDA.

The model is formulated as follows:

$$\text{logit}(p(d)) = \log(\alpha) + \beta \cdot \log(d/d^*),$$

where  $\text{logit}(p) = \log(p/(1-p))$ .  $p(d)$  represents the probability of having a DLT in the first cycle at dose  $d$ ,  $d^* = 1$  mg/kg is the reference dose, allowing for the interpretation of  $\alpha$  as the odds of a DLT at dose  $d^*$ , and  $\theta = (\log(\alpha), \log(\beta))$  with  $\alpha, \beta > 0$  is the parameter vector of the model. Standardized doses will be used such that one of the doses ( $d^*$ ) equals 1, e.g. doses are rescaled as  $d/d^*$ . As a consequence,  $\alpha$  is equal to the odds of the probability of toxicity at  $d^*$ .

Since a Bayesian approach is applied, a prior distribution  $\pi(\theta)$  for the unknown parameter vector  $\theta$  needs to be specified. This prior distribution will be specified as a normal distribution, i.e.

$$\pi(\theta) = \text{MVN}(\mu, \Sigma)$$

mean vector  $\mu$  and covariance matrix  $\Sigma$ , with

$$\Sigma_i = \begin{pmatrix} \sigma_{i,11}^2 & \sigma_{i,11}\sigma_{i,22}\rho_i \\ \sigma_{i,11}\sigma_{i,22}\rho_i & \sigma_{i,22}^2 \end{pmatrix}$$

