**Table 23. Summary of Prior Distribution**

| Mean Vector    | STD Vector | Correlation |
|----------------|------------|-------------|
| -2.685; -0.594 | 2; 0.5     | 0           |

STD, standard deviation.

A summary of the prior probabilities of DLT at different doses, as well as the corresponding probability of under, targeted and overdosing, are shown in Table 24. Graphically, the prior medians with accompanying 95% credible intervals (CrI) are shown in Figure 3. The uncertainty around the medians is large, showing the low amount of in-human information this prior provides.

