#### **9.4.1.5 Statistical Model Assessment**

The model was assessed using two different metrics:

- Hypothetical data scenarios: for various potential data constellations as they could occur in the current study, the maximal next doses as allowed by the model and by the 200% escalation limit are investigated. Data scenarios thus provide a way to assess the 'on-study' behavior of the model.
- Simulated operating characteristics: these illustrate for different assumed true dose-toxicity relationships, how often a correct dose would be declared as MTD by the model. They are a way to assess the 'long-run' behavior of the model.

In summary, the model showed very good behavior as assessed by these metrics. More details can be found in Appendix 12.8.

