### Hypothetical Data Scenarios

Hypothetical data scenarios are shown in Table 30. These scenarios reflect potential on-study data constellations and related escalation as allowed by the model and the 233% escalation limit (i.e. next higher dose is not higher than 3.33-fold of the highest dose already tested). For each scenario, the probability of overdose for the current dose, as well as the next potential dose and related probabilities of underdosing, target dose and overdosing are shown.

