|          | 3.00          | 1              | 3                  | 0.118         | 0.384                             | 3.00                  | 0.578         | 0.303         | 0.118         |
| 6        | 0.03          | 0              | 3                  |               |                                   |                       |               |               |               |
|          | 0.10          | 0              | 3                  |               |                                   |                       |               |               |               |
|          | 0.30          | 0              | 3                  |               |                                   |                       |               |               |               |
|          | 1.00          | 0              | 3                  |               |                                   |                       |               |               |               |
|          | 3.00          | 0              | 3                  |               |                                   |                       |               |               |               |
|          | 10.00         | 1              | 3                  | 0.155         |                                   | 10.00                 | 0.515         | 0.330         | 0.155         |

CONFIDENTIAL

May not be used, divulged, published, or otherwise disclosed without the consent of  
Molecular Partners AG, Schlieren, Switzerland

**Setting 3:** Describes the behavior if 2 in 3 patients experience a DLT at the current dose and 0 in 3 patients on lower dose levels. In all scenarios the model recommends to de-escalate.

| Scenario | Dose
mg/kg | Data -
#DLT | Data -
#Patient | CD -
P(OD) | Next
Higher
Dose -
P(OD) | Next
Dose
mg/kg | ND -
P(UD) | ND -
P(TD) | ND -
P(OD) |
|----------|---------------|----------------|--------------------|---------------|-----------------------------------|-----------------------|---------------|---------------|---------------|
| 1        | 0.03          | 2              | 3                  | 0.279         | 0.498                             | 0.01                  | 0.534         | 0.337         | 0.128         |
| 2        | 0.03          | 0              | 3                  |               |                                   |                       |               |               |               |

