**Table 32. Simulated Operating Characteristics**

| Scenario | % of Trials Declaring an MTD With True DLT Rate in |             |          | Max #Patient Reached Before MTD | Stopped     | #Patients        | #DLT             |
|----------|----------------------------------------------------|-------------|----------|---------------------------------|-------------|------------------|------------------|
|          | Underdose                                          | Target Dose | Overdose | % of Trials                     | % of Trials | Mean (min - max) | Mean (min - max) |
| 1(P)     | 9.4                                                | 68.4        | 16.4     | 4.4                             | 1.4         | 27.6 (3 - 45)    | 4.3 (2 - 10)     |
| 2(H)     | 2.4                                                | 61.0        | 20.8     | 0                               | 15.8        | 15.9 (3 - 33)    | 4.4 (2 - 9)      |
| 3(LH)    | 19.4                                               | 63.6        | 12       | 1.4                             | 3.6         | 22.1 (3 - 45)    | 4.4 (2 - 10)     |

DLT, dose-limiting toxicity; H, high-toxicity; LH, low-high-toxicity; MTD, maximum tolerated dose; P, probability.

In Scenario 1, which reflects the case that the true dose-toxicity is aligned with prior means, 68.4% of the simulated trials declared a dose as MTD with true DLT rate in the targeted dose range.

In Scenario 2 (high-toxicity scenario), the starting dose has already > 10% probability of observing at least 1 DLTs in the first cohort if 3 patients are enrolled. This contributes to the increased percentage of 15.8% of all simulated trials for which the trial is stopped since none of the doses are considered tolerable anymore. This is an expected situation for a high-toxicity scenario. Nonetheless, 61.0% of the simulated trials declared a dose as MTD with true DLT rate in the targeted dose range.

In Scenario 3, 19.4% of the simulated trials declared a dose as MTD with true DLT rate in the underdose dose range and in 1.4% of the trials, the MTD has not been found after 45 patients.

The proportion of trials where an overdose was declared as MTD was highest in scenario 2 with 20.8%. The mean patient numbers range from 15.9 patients (high scenario) to 27.6 patients (prior means scenario) and the maximum number of patients was 45, which is the maximum number of subject explored after which the simulation trials are stopped without declaring an MTD.

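### Table 30, Setting 3 Scenario 1 prints overdose probabilities that the protocol's own model does not give; on the model's figures no listed dose meets the 25% limit, so the de-escalation claim fails there

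*Protocol*

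**What the plan says.** Section 9.4.1.1 sets the overdose rule: "any dose of MP0317 that has more than a 25% chance of being in the excessive toxicity category is not considered for the next cohort". Excessive toxicity there means a true DLT rate of 33% or more.

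Appendix 12.8 illustrates the rule in Table 30. Setting 3 takes 2/3 DLTs at the current dose and 0/3 at each lower dose tested, and concludes: "In all scenarios the model recommends to de-escalate". Scenario 1 has data at 0.03 mg/kg only. It prints an overdose probability of 0.279 at 0.03 and 0.498 at the next higher dose, and names 0.01 mg/kg as the next dose with probabilities 0.534 / 0.337 / 0.128 for under-, target and overdosing. Setting 4b Scenario 1 continues from there with 0/3 at 0.01.

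Two statements in the surrounding text also matter. On the high-toxicity simulation, 12.8 says "the starting dose has already > 10% probability of observing at least 1 DLTs in the first cohort" if three patients are enrolled. On the escalation cap, 9.4.1.5 says "the maximal next doses as allowed by the model and by the 200% escalation limit are investigated", whereas 12.8 describes "escalation as allowed by the model and the 233% escalation limit".

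**The concern.** The data scenarios are one of the two metrics on which 9.4.1.5 and the end of 12.8 rest their favourable view of the model. Scenario 1 is the scenario that tests overdose control at the starting dose. If its printed probabilities belong to other data, the table shows a dose as admissible where the protocol's own rule excludes it, and the reader is told that the model always finds a lower dose when it does not.

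The page itself gives a warning. The current-dose column prints 0.279 in both Setting 3 Scenario 1 and Setting 4b Scenario 1, although the latter adds three DLT-free patients. In Scenarios 2 to 6 the same column falls between the two settings: 0.327 to 0.184, 0.269 to 0.168, 0.339 to 0.241, 0.411 to 0.308 and 0.482 to 0.376.

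**Working it through.** **Inputs.** Model (9.4.1.2): logit p(d) = log α + β·log(d/d*), with d* = 1 mg/kg. Prior (Table 23): log α and log β independent normal, means −2.685 and −0.594, standard deviations 2 and 0.5. Overdose: p(d) ≥ 0.33. Limit: P(overdose) at most 0.25.

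**Method.** Posterior ∝ prior × ∏ p(d)^x · (1 − p(d))^(n − x), integrated numerically on a fine grid. P(overdose at d) is the posterior mass where p(d) ≥ 0.33.

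**Step 1: reproduce the plan's own prior figures.**

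| Dose (mg/kg) | 0.01 | 0.03 | 0.10 | 0.30 | 1 | 3 | 10 |
|---|---|---|---|---|---|---|---|
| Table 24 | 0.020 | 0.032 | 0.054 | 0.091 | 0.166 | 0.267 | 0.401 |
| Recomputed | 0.019 | 0.031 | 0.053 | 0.090 | 0.162 | 0.263 | 0.396 |

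Settings 1 and 2, Setting 3 Scenarios 2 to 6, Setting 4a and the next-dose overdose column of Setting 4b also reproduce within about 0.015, apart from the cells listed in Step 4. The set-up is therefore right.

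**Step 2: Setting 3 Scenario 1.**

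| P(overdose) at | 0.01 | 0.03 | 0.10 |
|---|---|---|---|
| Printed | 0.128 | 0.279 | 0.498 |
| Model, 2/3 at 0.03 | 0.370 | 0.532 | 0.706 |
| Model, 2/3 at 0.03 plus 0/3 at 0.01 | 0.123 | 0.268 | 0.491 |

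For the stated data, the three probabilities at 0.01 mg/kg are 0.311 / 0.320 / 0.370. With the added 0/3 they are 0.547 / 0.329 / 0.123, close to the printed 0.534 / 0.337 / 0.128. The row matches the Setting 4b data. Since 0.370 > 0.25 at the lowest listed dose and the model is increasing in dose, no listed dose is admissible. Importance sampling with 4 million prior draws gives the same result (0.370, 0.532, 0.705).

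**Step 3: compare with Table 32.** Assuming a first cohort of three in the simulations, P(at least 2 DLTs) = 3q²(1 − q) + q³ at 0.03 mg/kg. With q = 0.05, 0.2 and 0.1 this is 0.7%, 10.4% and 2.8%. The stopped trials are 1.4%, 15.8% and 3.6%, somewhat above these figures, with a minimum of 3 patients and 2 DLTs. P(3 of 3) is only 0.01%, 0.8% and 0.1%. This suggests that the simulation stopped after 2/3 at the starting dose, where Table 30 continues.

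**Step 4: cells and statements that change no decision shown.**

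- Setting 3 Scenario 5, next dose 1.00: 0.579 + 0.350 + 0.007 = 0.936. The model gives 0.069 for the last term.
- Setting 1 Scenario 3: 1.00 mg/kg has 0.063 in the next-higher column and 0.032 in the next-dose column; model 0.031.
- Setting 4a Scenario 2 (1.00 mg/kg): 0.145 against 0.208; model 0.202. Scenario 3 (3.00 mg/kg): 0.174 against 0.242; model 0.237. The next-dose cells are the ones the model supports.
- Setting 4b, current-dose column: printed 0.279, 0.184, 0.168, 0.241, 0.308, 0.376. At the dose that earlier had 2/3 DLTs the model gives 0.268, 0.177, 0.164, 0.242, 0.308, 0.376. At the dose last given it gives 0.123, 0.041, 0.024, 0.017, 0.024, 0.030.
- High-toxicity text: with q = 0.2 and n = 3, P(at least 1) = 1 − 0.8³ = 48.8%; P(at least 2) = 10.4%.
- Escalation cap: Table 3 plans q3w steps of +233% from 0.03 to 0.10, 0.30 to 1.00 and 3.00 to 10.00 (10/3 = 3.33-fold). A 200% cap would exclude all three.

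**The case against.** The strongest reply is that Table 30 is illustrative. The model is refitted at each escalation step, and under 8.5 the dose-escalation committee (DERC) reviews the current model summaries. Sections 6.3 and 12.6 record a review of the first two q3w cohorts on 9 March 2022, before Version 4.0 of 21 April 2022, so the Scenario 1 row is no longer live for q3w. Under 9.4.1.4 the q1w schedule gets its own prior and scenarios in the SAP. All of this stands and limits the consequence; it does not make the row or the sentence correct.

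A different prior could be suggested as the cause. A standard deviation of 1.5 for log α, or reading the Table 23 entries as variances, brings 0.01 mg/kg to 0.186 or 0.201. Both readings contradict Table 23, and neither yields 0.128 / 0.279 / 0.498.

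Three stronger readings are tempting, and the protocol does not support them:

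- **That Setting 4b is impossible**, because 1.00 mg/kg appears to carry 0.308 while 2.00 carries 0.163. The 0.308 is the model's value for 3.00 mg/kg, the earlier toxic dose. The column is unclearly labelled; its values are the model's.
- **That the 10% statement is false.** 48.8% does exceed 10%, so it is literally true. It is loose, and the figure fits at least two DLTs.
- **That the committee would dose from Table 30.** Nothing in 5.2.7, 8.5 or 9.13 says so.

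**Conclusion.** The point holds for Setting 3 Scenario 1. The printed overdose probability at 0.01 mg/kg is 0.128 and the model's is about 0.37, against a limit of 0.25. The claim of de-escalation in all scenarios is false for that row, and Setting 4b Scenario 1 starts from a step that the rule in 9.4.1.1 would have excluded. The discrepancy is far beyond the differences of up to about 0.015 seen elsewhere.

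This rests on the model, reference dose and prior as printed in 9.4.1.2 and Table 23, which reproduce Table 24. That the row was computed on the Setting 4b data is inferred from the numerical match. That the simulations stopped after 2/3 at the starting dose is a plausible inference from Table 32, not something 12.8 states. A reader might infer that the operating characteristics are wrong too; the comparison in Step 3 points the other way.

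The remaining cell errors, the unclear label, the loose 10% sentence and the 200% against 233% conflict are minor and alter no decision shown. What needs correcting is the stated evidence on model behaviour, not a pending q3w dose decision.

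**What to change.** Recompute every cell of Table 30 from the Table 23 prior, with the data behind each row checked, and correct the Setting 3 sentence for Scenario 1. Relabel or recompute the Setting 4b current-dose column. Restate the 10% sentence so that the number of DLTs and the probability agree.

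Reconcile Setting 3 Scenario 1, Setting 4b Scenario 1 and the dose level −1 text in 5.2.7.1 and Table 3 with the 25% limit in 9.4.1.1. Reconcile the 200% limit in 9.4.1.5 with the 233% in 12.8 and Table 3. Which clinical action applies is for the sponsor and the committee to settle; this review proposes none.

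Check the q1w data scenarios planned for the SAP for the same errors. The cost is a re-tabulation from existing code and a correction to the appendix and a few sentences; no new data are needed.

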## Operating Characteristics

Operating characteristics are a way to assess the long-run behavior of a model. Under an assumed true dose-toxicity curve, metrics such as the probability of recommending a dose with true DLT rate in the target interval can be approximated via simulation. Table 31 describes 3 assumed true dose-toxicity scenarios which were used to assess the operating characteristics of the model. These scenarios reflect a wide range of possible cases as follows:

- Scenario 1 (P): Aligned with prior means
- Scenario 2 (H): High-toxicity scenario
- Scenario 3 (LH): Low-toxicity followed by high-toxicity

**Table 31. Assumed True Dose-Toxicity Scenarios**

| Scenario |              |      |            |            |            |             |             |      |
|----------|--------------|------|------------|------------|------------|-------------|-------------|------|
|          | Dose (mg/kg) | 0.01 | 0.03       | 0.10       | 0.30       | 1.00        | 3.00        | 10   |
| 1(P)     | P(DLT)       | 0.03 | 0.05       | 0.07       | 0.1        | 0.16 | 0.23 | 0.33 |
| 2(H)     |              | 0.1  | 0.2 | 0.3 | 0.4        | 0.5         | 0.6         | 0.7  |
| 3(LH)    |              | 0.05 | 0.1        | 0.15       | 0.2 | 0.25 | 0.4         | 0.45 |

Bold numbers indicate true DLT rates in the target interval [0.16-0.33).

DLT, dose-limiting toxicity; H, high-toxicity; LH, low-high-toxicity; P, probability.

For each of these scenarios, 500 studies were simulated. Thereby, in addition to the MTD definition in Section 5.2.7.2, the MTD is set to the RDE of 10 mg/kg (the highest considered dose) if 6 patients have been treated at 10mg/kg and the probability of overdosing is below 25% at this dose. On the other hand, if after at least 45 patients no MTD was found, the trial was stopped without declaring an MTD. It was then assessed how often a dose was declared as MTD with true DLT rate in the under-, targeted or over-dose range. Furthermore, the average, minimum and maximum number of patients per study and the average number of DLTs per study are reported. Results are shown in Table 32.

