### 5.2.7.2 MTD Definition

The MTD is defined as the highest dose of study drug where the posterior probability of the true DLT rate in the target interval [0.16 to 0.33] of the MTD is above 0.50 with less than 25% risk of the true DLT rate being above 33%, and at least 6 patients have been treated in a confirmatory cohort of patients for the duration of the DLT evaluation period (Section 5.2.6).

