### 9.1 Sample Size Determination

Up to 6 provisional dose levels are planned for this study with at least 1 to 3 patients per dose level. It is estimated that between 17 and 30 patients will be included for the dose-escalation part of the q3w schedule, and 12 to 18 patients for the dose-escalation part of the q1w schedule. Up to 15 patients treated at the RDE (or MTD) will be included in the safety expansion part of each dosing schedule giving a total of between 32 and 78 patients. The actual number of patients will depend on the number of dose levels/cohorts that are tested, the number of patients considered non-evaluable for the DDS and who are replaced, and the safety profile seen at each dose level.

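### Appendix 12.8 does not describe the planned q3w escalation consistently: Table 32 contradicts the 10 mg/kg rule stated for it, gives no result at the planned size, and one Table 30 row does not follow from the model

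*Protocol*

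**What the plan says.** **Size.** Section 9.1 reads "It is estimated that between 17 and 30 patients will be included for the dose-escalation part of the q3w schedule"; Section 3.2 and the summary give the same range. The Table 3 maxima for q3w cohorts 1 to 6 sum to 3+3+6+6+6+6 = 30. Appendix 12.8 simulates further: "if after at least 45 patients no MTD was found, the trial was stopped without declaring an MTD". Table 32 shows maxima of 45, 33 and 45 patients in scenarios 1 to 3.

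**Stopping rules.** The MTD definition (5.2.7.2) sets this condition: "the posterior probability of the true DLT rate in the target interval [0.16 to 0.33] of the MTD is above 0.50". It also asks for an overdose risk below 25% and at least 6 patients. Appendix 12.8 adds a rule for the simulation: "the MTD is set to the RDE of 10 mg/kg (the highest considered dose) if 6 patients have been treated at 10mg/kg". This applies only when overdose probability at that dose is under 25%. The number of runs is given too: "For each of these scenarios, 500 studies were simulated".

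**Results.** Table 32 prints target-range selection of 68.4%, 61.0% and 63.6%, and a minimum of 2 DLTs per trial in every scenario. The appendix closes by calling the precision of MTD determination good.

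**Data scenarios.** Above Table 30 Setting 3 (2 of 3 patients with a DLT at the current dose) stands: "In all scenarios the model recommends to de-escalate". Section 9.4.1.1 sets the overdose limit: "any dose of MP0317 that has more than a 25% chance of being in the excessive toxicity category is not considered for the next cohort".

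**The concern.** Determining the RDE or MTD is a primary objective, and Appendix 12.8 is the only evidence of accuracy given for the q3w model. Three things do not fit together. The accuracy figures come from a design allowed to run half as long again as the planning range. One stopping rule in the text seems incompatible with a figure in the results table. One data scenario shows the model allowing a dose that the stated model would exclude. If so, the favourable summary belongs to a design other than the one described, and the chance of declaring an overdose as MTD is understated in the scenario built on the sponsor's own prior.

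**Working it through.** **Inputs.** Logistic model with reference dose 1 mg/kg (9.4.1.2); prior means −2.685 and −0.594, SDs 2 and 0.5, correlation 0 (Table 23); 25% overdose limit (9.4.1.1); MTD criteria (5.2.7.2); true DLT rates (Table 31). Cohorts of 3 are assumed, because the simulated cohort size is not stated.

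**Reproducing the plan first.** The prior overdose probabilities at 3 and 10 mg/kg come out at 0.262 and 0.397 (Table 24: 0.267 and 0.401). Table 30 Setting 3 scenario 3 comes out at 0.268 and 0.070 (printed 0.269 and 0.071). The model is therefore the one described.

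**1. The 10 mg/kg rule against the minimum of 2 DLTs (scenario 1).** Table 30 itself shows that the rule must fire. With no DLT below, the overdose probability at 10 mg/kg is 0.018 after 0/3, 0.155 after 1/3 and 0.051 after 1/6. All are below 0.25, so the trial stays at 10 mg/kg and ends at 6 patients. After 1/6 the target probability is only 0.255, so the ordinary MTD criterion is not met and only the added rule applies. After 0/6 the overdose probability is 0.005.

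- No DLT in five lower cohorts of 3: (0.95 × 0.93 × 0.90 × 0.84 × 0.77)³ = 0.5143³ = 0.1360
- Then 0/6 at 10 mg/kg: 0.1360 × 0.67⁶ = 1.23%
- Then 1/6 at 10 mg/kg: 0.1360 × 6 × 0.33 × 0.67⁵ = 3.64%
- Sum: 4.87%, or 500 × 0.0487 ≈ 24 trials with 0 or 1 DLT
- Chance of no such trial in 500: (1 − 0.0487)⁵⁰⁰ ≈ 1.5 × 10⁻¹¹

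Other low-DLT paths bring the simulated share to about 6–7%. Re-simulated scenario 1, cap 45:

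| | Target % | Overdose % | Mean DLTs | Minimum DLTs |
|---|---|---|---|---|
| Table 32 | 68.4 | 16.4 | 4.3 | 2 |
| Rule left out | 65.0 | 16.2 | 4.5 | 2 |
| Rule as written | 61.2 | 21.2 | 4.0 | 0 |

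A second implementation gave target 67.0% and overdose 17.5% without the rule, and overdose 21.2% with it.

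**2. Size.** Re-simulation with at most 30 patients, cohorts of 3:

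| Scenario | Table 32 target % | Cap 30, rule on | Cap 30, rule off | No MTD at the cap (Table 32; on; off) |
|---|---|---|---|---|
| 1 | 68.4 | 45.7 | 48.4 | 4.4; 22.7; 30.7 |
| 2 | 61.0 | 61.7 | 61.7 | 0; 0.3; 0.3 |
| 3 | 63.6 | 58.4 | 58.4 | 1.4; 10.1; 10.5 |

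Like for like, moving the cap from 45 to 30 costs scenario 1 61.2 − 45.7 = 15.5 points with the rule and 65.0 − 48.4 = 16.6 without it. Other implementations and readings of the unstated details put scenario 1 at roughly 42–55% target and about 17–36% without an MTD. With one patient in each of the first two cohorts it is 52.3% target with the rule, and 13.8% reach the cap. At cap 45, between 18% and 31% of scenario 1 trials need more than 30 patients in most runs.

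**3. Table 30, Setting 3, scenario 1 (2/3 DLTs at 0.03 mg/kg).**

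| Overdose probability at | 0.01 | 0.03 |
|---|---|---|
| Printed | 0.128 | 0.279 |
| Stated model, 2/3 at 0.03 | 0.37 | 0.53 |
| Same, plus 0/3 at 0.01 | 0.123 | 0.267 |

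The printed row matches data that include three further patients at 0.01 mg/kg who belong to Setting 4b. The protocol shows this itself. Setting 4b, which does include them, prints the same 0.279 for scenario 1. In the other five scenarios the value at the dose where the DLTs occurred falls between the two settings (0.327 to 0.184, 0.269 to 0.168, 0.339 to 0.241, 0.411 to 0.308, 0.482 to 0.376). At 0.37, the 0.01 mg/kg dose also exceeds the 25% limit.

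Table 32 points the same way. It reports trials of 3 patients in scenario 1. If 2/3 led on to another cohort, only 3/3 could end a trial there: 0.05³ × 500 ≈ 0.06 trials expected.

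**The case against.** Several points on the other side stand.

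- The range 17–30 is an estimate. Section 9.1 ties the actual number to cohorts tested and replacements, and Section 5.2.7.1 allows cohorts and dose levels to be added. A reader might infer that 30 is a protocol ceiling; it is not.
- The cap of 45 is disclosed, and it is a cap. The simulated means are 27.6, 15.9 and 22.1, all below 30.
- A reader might count every trial without an MTD as a failed primary objective. The objective is the RDE or the MTD, and Sections 5.2.7.3 and 8.5 provide for a dose when no MTD is reached.
- A reader might conclude that the 10 mg/kg rule was left out of the code. That is inference: the text says it was applied, and a wrong minimum in the table cannot be excluded. The fit without the rule is also imperfect: underdose selection is 13.0% against 9.4% printed, about 2.4 standard errors of a 500-trial run.
- That trials stop after 3 patients with 2 DLTs is pieced together from separate minimum columns; Table 32 does not state it.
- Cohort decisions use the live posterior, the overdose limit and committee review, so Table 32 does not itself set any patient's dose.

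None of this removes the contradiction between rule and table or the error in the Table 30 row. Neither depends on how many patients are enrolled.

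**Conclusion.** The concern holds in three limited parts.

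1. The stated 10 mg/kg rule and Table 32's scenario 1 minimum of 2 DLTs cannot both be right. With the rule, overdose selection in scenario 1 is about 21% rather than about 16–17%.
2. No accuracy result is given at the planned size. Ending at 30 would lower scenario 1 target selection to roughly 42–55% and scenario 3 by about 4–8 points. The cap hardly touches scenario 2.
3. The Table 30 row does not follow from the stated model, and for that row the sentence on de-escalation conflicts with the 25% limit in Section 9.4.1.1.

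The broader reading, that the planned escalation lacks the claimed accuracy throughout, is not supported. Part 2 rests on treating 30 as the stopping point and on simulation details the protocol does not state, so no single replacement figure can be prescribed. Part 1 assumes cohorts of 3. Part 3 needs only the published model and prior.

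**What to change.** - Re-run Table 32 with the rules as stated, giving cohort size and the exact MTD check, and report results at 30 patients alongside 45. Alternatively, align the rule text and the estimated q3w size (Sections 3.2, 9.1 and the summary) with what was simulated. An upper q3w figure of 45 would make the maximum total 45 + 18 + 15 + 15 = 93 instead of 78.
- Print the sponsor's own re-run figures, and restate the conclusion on precision by scenario.
- Recompute Table 30 Setting 3 scenario 1. Reconcile the sentence above it with the overdose limit in Section 9.4.1.1 and with Table 32.

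The cost is a few hours of simulation and less favourable figures for scenarios 1 and 3. Restating the tables needs no extra patients.
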